**APPENDIX I**

**Relapsing-Remitting MS:**

Relapsing-remitting MS is characterized by clearly defined acute attacks with full recovery, or with sequlae and residual deficit upon recovery. ([name] and [name]. Defining the clinical course of multiple sclerosis. Neurology 1996; 46:907-911).

**Relapse Documentation Prior to Study Entry**

Every attempt will be made to obtain documentation of relapses which occurred one year prior to study entry. If no written documentation is available, the Investigator will contact the patient’s physician by phone in order to obtain all information of the patient’s relapses. This should be documented as a phone-call report.

**Definition of Relapse During the Study**

The following: “ relapse,” exacerbation,” “attack,” and “ bout” are equivalent terms. The term “**relapse**” will be used through this Protocol. A relapse is defined as the appearance of one or more new neurological abnormalities or the reappearance of on or more previously observed neurological abnormalities. This change in clinical state must last at least 48 hours and be immediately preceded by a relatively stable or improving neurological state in the 30 days before deterioration. An event is counted as a relapse only when the patient’s symptoms are accompanied by observed objective changes on the neurological examination consistent with an increase of at least 0.5 on the EDSS or one grade in the score for two or more of the seven functional systems (FS) of Kurtzke or two grades in the score for one of the FS and compared to the previous evaluation. The patient must not be undergoing an acute metabolic change such as fever or other medical abnormality and a change in bowel, bladder, or in cognitive function must not be entirely responsible for the changes in EDSS or FS scores.

**APPENDIX II**

**Instructions for Testing Lower Extremity Function:**

**Timed 10 Metter Walk**

MATERIAL NEEDED Stopwatch, 10 meter Walk Source Document Form,

Marked 10 meter distance in an unobstructed hallway,

Assistive Device (if needed)

TIME LIMIT PER TRIAL 3 minutes (180 seconds) per trial.

DISCONTINUE RULES 1) If the patient cannot complete a trial in 3 minutes

2) If the patient cannot complete Trial #2 of the Timed Walk after a 5 minute rest

ADMINISTRATION

*Trial 1*:

Make sure that the stopwatch is set to “0.” For the Timed 10 meter Walk, the subject should be directed to one end of a clearly marked 10 meter course (clearly defined on the floor or on the wall) and instructed to stand just behind the starting line. Point out where the 10 meter course ends, then instruct the patient as follows: “*I’d like you to walk 10 meter* *as quickly as possible, but safely. Do not slow down until after you’ve passed the finish line. Ready” Go.”*

Begin timing when the lead foot is lifted and crosses the starting line. The examiner should walk along with the patient as s/he completes the task. Stop timing when the lead foot crosses the finish line. The examiner should then record the subject’s walk time to within 0.1 second, round as needed. Round up to the next tenth if hundredths place is >0.05, round down if hundredth place is <0.05 (*e.g.* 32.45” would be rounded up to 32.5”, but 32.44” would be rounded down to 32.4”). Once the time is recorded, be sure to reset the stopwatch to “0.”

*Trial 2*:

After completing the first timed walk, position the patient just behind the line where s/he is now standing, repeat the same instructions, and have the patient complete the walk again.

*Assistive Devices*:

The goal is to use the same assistive device on each study visit. The patient will use any assistive device that s/he uses routinely, keeping in mind that the patient may deteriorate modestly during the trial. The study coordinator will enter this device on the Source Document Form. In general, patients should use their customary assistive devices(s), NOT the least assistive possible, to complete the test. For patients with significant gait impairment, the treating neurologist should have the patient use a rolling walker, even if this is not the patient’s customary device. Non-wheeled walkers may be used if this is the customary assistive device used by the patient.

COMPLETING THE SOURCE DOCUMENT FORM

*In the space provided on the source Document Form, record any circumstances that you believe may have affected the patient’s performance. These are factors that may have affected the trial, but were not severe enough to necessitate repetition of the trial. Examples include, but are not limited to the following:*

- *The patient had a cold or reports not feeling well;*
- *The patient tripped but did not fall.*

If a situation a situation arises that necessitates the repetition of a trial, check “Yes” for the question, “Did it take more than two attempts to get two successful trials?” and then specify the reason why a trial had to be repeated. Examples of reasons to repeat a trial include, but are not limited to, the following:

- The patient feel during the walk;
- The examiner forgot to start or to stop the stopwatch;
- The examiner forgot to reset the stopwatch between trials;
- The patient stopped to talk to someone while walking, or another person/thing somehow interfered with the walk.

**Record only the times for the**

**two successfully completed trials of the Timed 10 meter Walk.**

If the patient could not complete one or both of the trials for the Timed 10 meter Walk, record this in the appropriate section of the Source Document Form. If the patient’s disease has progressed and/or physical limitations prohibit him or her from completing the trial, you should check the box for “Unable to complete trial due to physical limitations.” Then record any specifics that you can observe (*i.e.*, patient is in a wheelchair now and is unable to walk, *etc.*). If the patient did not complete a trial for any other reason, check the box for “Other” and record the specific circumstances (*e.g.*, patient feel and was too fatigued to complete another trial, patient refused to complete trial).

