**Primary Safety Endpoint**

The primary safety endpoint for this study are the safety profile of adverse experiences, the tolerability will be based on the number of patients completing the study.

- 1. **Secondary Efficacy Endpoints:**

Changes from the baseline of clinical parameter; 10 meter walking test, 9-Hole-peg Test, PASAT cognition test and the Ambulatory Index (AI).

The total number of T1-Gd enhancing lesions (in MRI) and of T1 hypo dance black holes.

The volume of T2 lesions: (in MRI) and the degree of brain atrophy i.e. BPF (brain parenchymal factor) width corpus colossus and of lateral ventrical).

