**6.2.1 Inclusion Criteria**

To be eligible for inclusion into the study, each patient must fulfill the following criteria:

1. Clinically definite MS of the relapsing-progressive type (RPMS) according to Poser’s criteria (16).

2. Age; 18-60 years old, inclusive.

3. EDSS: 3.0 to 6.5, inclusive

4. Disease duration: above one year.

5. Evidence of disease progression of 1 degree in the EDSS scale, or at least two severe relapses (needed hospitalization and treatment) during the last year prior to inclusion.

6. MRI of the brain with at least 5 lesions in the white matter (T2 imaging).

7.Failure of other existing treatments according to the guidelines of the Israeli Ministry of Health.

8. All patients will sign the written informed consent form.

9. Males and female (birth control, where appropriate)

10. Patients that their T cells will respond, and be activated by the myelin-derived peptides and a specific T-cell-vaccine can be produce for them.

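### The 10 meter walk endpoint gives no value to a patient who can no longer complete it, so a known worst result is dropped or may be replaced by an earlier, better time

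*Protocol*

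**What the plan says.** Section 4, Secondary Efficacy Endpoints, lists "Changes from the baseline of clinical parameter; 10 meter walking test, 9-Hole-peg Test, PASAT cognition test and the Ambulatory Index (AI").

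Appendix II sets out how the walk is tested. The limit is "3 minutes (180 seconds) per trial", and a patient who has not finished by then is stopped. The form is to hold times only for the "two successfully completed trials of the Timed 10 meter Walk". For failures the instruction is: "If the patient could not complete one or both of the trials for the Timed 10 meter Walk, record this in the appropriate section". One box covers disease progression or physical limitation, with a patient now in a wheelchair as the example. A separate box covers any other reason. Neither box carries a value, and neither does passing the time limit.

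Section 12, on analysis cohorts and missing data, gives one rule: LOCF in the ITT cohort, where judged appropriate, for data missing at or before month 12. No rule is given for the Completers or Evaluable cohorts.

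Section 6.2.1 admits patients with "EDSS: 3.0 to 6.5, inclusive", after one EDSS degree of progression or two severe relapses in the preceding year.

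On walking aids, Appendix II says "The goal is to use the same assistive device on each study visit". For significant gait impairment it adds that "the treating neurologist should have the patient use a rolling walker", customary or not. The device used is entered on the form.

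**The concern.** A change from baseline needs a value at both ends. A patient who attends month 12 and cannot walk 10 meters has been assessed, and the result is the worst the test can give. The protocol turns that result into a ticked box and then offers only a rule for missing data.

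The case is foreseeable. Entry extends to EDSS 6.5 in patients with recent worsening, and Appendix II itself describes the patient who now needs a wheelchair. If the arms differ in how many patients lose the walk, the arm that does worse has more of its worst results removed or softened. A true benefit on walking is then understated, and a true harm can be hidden. With 10 placebo and 20 vaccine patients, a few such cases can move the comparison materially.

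**Working it through.** The protocol states no power, event rate or standard deviation for the walk, so there is no figure to reproduce. The check has two parts.

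**1. Following the text for one patient.** Suppose a patient has a baseline time, attends every visit and cannot walk at month 12.
- Appendix II: physical-limitation box ticked, no time entered.
- Section 4: the change from baseline cannot be computed.
- Section 12, ITT cohort: if LOCF is judged appropriate, the last time at which the patient could still walk is used; if not, the patient has no result.
- Section 12, Completers cohort: the patient belongs to it, has no walk result, and no rule applies.

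No branch records the inability as the outcome of this test.

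**2. Size, by illustration only.** Arm sizes (10 and 20), the 180 s limit and two-sided 5% come from the protocol. All loss rates and walk times below are assumptions.

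Chance of at least one such patient among 30, at a one-year loss rate p, is 1 - (1 - p)^30:
- p = 5%: 1 - 0.95^30 = 78.5% (expected number 1.5)
- p = 10%: 1 - 0.90^30 = 95.8% (expected 3)
- p = 20%: 1 - 0.80^30 = 99.9% (expected 6)

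Simulation, 4000 trials per row. Baseline time is log-normal with median 20 s and log-SD 0.5. Change among walkers is +2 s (SD 4) in both arms. The last change before losing the walk is +4 s. Entries are vaccine minus placebo in mean change, in seconds:

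| Loss, placebo / vaccine | Dropped | LOCF | Scored at 180 s |
|---|---|---|---|
| 10% / 10% | 0.0 | 0.0 | 0.0 |
| 10% / 5% | 0.0 | -0.1 | -7.7 |
| 20% / 5% | 0.0 | -0.3 | -22.9 |
| 30% / 10% | 0.0 | -0.4 | -30.6 |
| 40% / 10% | 0.0 | -0.6 | -46.3 |
| 10% / 30% (harm) | 0.0 | +0.4 | +31.5 |

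A hand check of the 30% / 10% row agrees. Under LOCF: (0.10 - 0.30) x (4 - 2) = -0.4 s. At 180 s, mean baseline is 20 x exp(0.125) = 22.7 s, so (0.10 - 0.30) x (180 - 22.7 - 2) = -31.1 s, against -30.6 s simulated.

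In that row a rank test rejects in 4.5% of trials when non-walkers are dropped, 5.2% under LOCF and 13.3% when they are scored at the limit.

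The same point in speed, for one patient with assumed times of 20 s at baseline, 30 s at month 10 and inability at month 12:
- LOCF change: 10/30 - 10/20 = 0.33 - 0.50 = -0.17 m/s
- Change with inability scored as zero: 0 - 0.50 = -0.50 m/s
- Understatement: 0.33 m/s

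With 2 of 10 placebo and 1 of 20 vaccine patients affected, the difference between arms is understated by 0.33 x 2/10 - 0.33 x 1/20 = 0.067 - 0.017 = 0.05 m/s.

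**The case against.** The strongest objection is that scoring a failed timed test is ordinary content of a statistical analysis plan, which is not at hand. On this view Appendix II governs administration and form-filling, not analysis. The line limiting entries to completed times follows text on repeated attempts and may mean only that spoiled attempts are not entered. LOCF is discretionary, and nothing says an inability must count as missing. The endpoint's unit is not stated either.

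Much of this stands. An analysis plan could still assign a worst score, and the reason for failure is kept on the form. What remains is that the protocol foresees this patient, yields only times for the endpoint, and states one rule for a gap; for this patient that rule gives a wrong value.

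It also stands that loss of walking is captured elsewhere. EDSS is the primary efficacy measure, and Ambulation Index grades 7 to 9 (Appendix III) describe inability to walk 25 feet and wheelchair restriction. The damage is confined to one secondary measure.

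Two stronger readings are tempting and not supported. A reader might infer that one or two cases decide the comparison. For 2 of 10 against 1 of 20, Fisher's exact test on the loss itself gives (900 + 120)/4060, p = 0.25, and even at 30% against 10% the worst-value score rejects in only 13.3% of simulated trials. A reader might also infer that the device text contradicts itself. It is worded as a goal with an express exception for significant gait impairment, so it can be followed as written. What it leaves open is only how a time taken with a changed device is handled.

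**Conclusion.** The concern holds for the secondary walk endpoint. As written, a patient who cannot finish because of disease progression, or who passes 180 s, is left out or may be given an earlier, better time, although the outcome was observed. The direction of the bias depends on which arm loses more walkers; if the loss is equal, the illustration shows none. Its size cannot be derived from the protocol, and every figure in seconds or m/s above rests on assumed loss rates and times. The primary EDSS endpoint and the Ambulation Index are not affected. This should be corrected, but it does not threaten the trial's main conclusion.

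**What to change.** Add one scoring rule to the protocol:
- Inability to complete because of physical limitation, and passing the 180 s limit, are observed worst outcomes.
- They take the worst rank in a rank-based comparison of change (or 0 m/s if the walk is analysed as speed).
- They are excluded from LOCF.
- Only failures ticked under the other-reasons box are treated as missing.
- State which rule applies when only one of the two trials is completed.

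Flag in the analysis any visit at which the device differs from baseline; the form already records it.

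The cost is a few sentences. The form already separates physical limitation from other reasons, so no new data are needed. The one drawback is that a rank analysis gives a less direct estimate of effect in seconds; reporting the number unable to complete in each arm beside it would help the reader.

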**APPENDIX III**

**Ambulation Index**

| **Grade** | **Condition** |
| --- | --- |
| 0 | Asymptomatic; fully active. |
| 1 | Walks normally, but reports fatigue that interferes with athletic or other demanding activities. |
| 2 | Abnormal gait or episodic imbalance; gait disorder is noticed by family and friends; able to walk 25 feet (7.5 meters) in 10 seconds or less. |
| 3 | Walks independently; able to walk 25 feet in 20 seconds or less. |
| 4 | Requires unilateral support (cane or single crutch) to walk; walks 25 feet in 20 seconds or less. |
| 5 | Requires bilateral support (cane, crutches, or walker) and walks 25 feet in 20 seconds or less; or requires unilateral support but needs more than 20 seconds to walk 25 feet. |
| 6 | Requires bilateral support and more than 20 seconds to walk 25 feet; may occasionally use wheelchair. |
| 7 | Walking limited to several steps with bilateral support; unable to walk 25 feet; may use wheelchair for most activities. |
| 8 | Restricted to wheelchair; able to transfer self independently. |
| 9 | Restricted to wheelchair, unable to transfer self independently. |

The use of a wheelchair may be determined by lifestyle and motivation. It is expected that patients in Grade 7 will use a wheelchair more frequently than those in Grade 5 or Grade 6. Assignment of a grade in the range of 5 to 7, however, is determined by the patient’s ability to walk a given distance, and not by the extent to which the patient uses a wheelchair.

**APPENDIX IV**

**Magnetic Resoncance Imaging (MRI) Protocol**

T1-weighted (after Gadolinium injection) and dual-echo MRI scans of the brain will be performed. MRI will be acquired twice, *i.e.* at the baseline visit and at study termination. Therefore, the second MRI scan will be obtained 12 months after the baseline MRI scan.

Baseline MRI scans should always be obtained within 72 hours from the clinical baseline assessment.

The scanner is of 2.0 Tesla magnetic field strength.

Scanning Requirements

Given the importance of careful repositioning for serial MRI lesion counting and load assessments, great care should be taken when positioning the patients in the scanner and head holder. The following rules apply to all the centers:

- Check that the patient can successfully undergo MRI examination;

- Enter the patient data into the scanner console, using:

- - Patient’s initials;
  - Study number (protocol number, center number, patient number)
  - Date of birth
  - Sex
  - Weight
  - Scan number (use progressive numbers starting from 1 for the baseline scan, so for the project, scan #1 or scan #2).

- Explain the scanning procedure to the patient and position her/him in the scanner in the most comfortable position.

- **Insert an intravenous needle in the patient’s arm and connect it with a long-line catheter to a drip-infusion of saline; for contrast injection, the operator will be able to use the long-line without moving the patient table from the scanner.**
- Position the patient’s head, and align it in the machine using land-marking devices provided with most of the equipment;
- Position the patient’s eyebrows at the center of the coil, and make sure that the horizontal light beam runs over the eyebrows and as close as possible to the line marking the coil center;
- Position the patient’s nose along the Z axis of the scanner, *i.e.*, make sure that the vertical light beam runs over the nose;
- To avoid patient’s had movement, fix it with foam cushions and foal strips;
- Move the patient into the scanner;

Imaging:

The following order for sequences will be kept:

- T1-weighted axial scout;
- T1-weighted coronal scout;
- T1-weighted sagittal scout;
- Rapid T1-weighted SE or T2-weighted FSE/TSE axial scout (this is for repositioning check);
- T2-weighted FSE/TSE;
- T1-weighted SE post-gadolinium.

Sequences from 1-4 will be done to obtain reference images for patient repositioning.

Sequence parameters:

- TR: 100;
- TE: 10-20;
- Slice number: 3;
- Orientation: axial;
- Field of view (FOV): 210-230mm;
- Matrix: 128 x 256;
- Inter-slice gap: 5mm;
- Number of acquisitions: 1;
- Phase encoding: L > R.

Using sequence 1 as a reference, make a coronal scout, parallel to the brain transverse diameter and depicting the midline of the brain best (*i.e.* at the level of the brainstem); the acquisition parameters will be the following:

- TR: 100;
- TE: 10-20;
- Slice number: 1;
- Slice thickness: 5mm;
- Orientation: coronal;
- Field of view (FOV): 210-230mm;
- Matrix: 128-256;
- Number of acquisitions: 1;
- Phase encoding: L > R.

From the coronal scout, make a sagittal scout image, aligned with the *falx cerebri* and other midline structures, according to the following parameters:

- TR: 500-650;
- TE: 10-20;
- Slice number: 1;
- Slice thickness: 5mm;
- Orientation: sagittal;
- Field of view (FOV): 210-230mm;
- Matrix: 128 x 256;
- Number of acquisitions: 1-3;
- Phase encoding: A > P.

On the sagittal scout image previously obtained, position the axial image group, placing the center of the slice group at the inferior borders of the *corpus calosum genu* and *splenium*. The slice group will be positioned to include the whole brain from the vertex to the level of the *foramen magnum*. Save the localizer image with the slices shown on it, to achieve the same slice positioning on subsequent scans; then make a rapid series of either T-weighted or T2-weighted images (according to the site preference) in order to check the correct positioning of the slices.

For T1-weighted images, the following parameters should be used:

- TR: 600;
- TE: 10-20;
- Slice number: 22;
- Slice thickness: 3mm;
- Orientation: axial;
- Field of view (FOV): 250mm;
- Matrix: 140 x 256;
- Inter-slice gap: 3mm;
- Series: interleaved;
- Number of acquisitions: 1;
- Phase encoding: L > R.

For T2-weighted images, a fast spin echo (or turbo spin echo sequence should be used with the following parameters:

- TR: 1800-2000;
- TE: either single-echo or dual echo (according to the site preference):
  - TE first echo: 30-59;
  - TE second echo: 60-100;
- ETL: according to site preference;
- Slice number: 22;
- Slice thickness: 3mm;
- Orientation: axial;
- Field of view (FOV): 250mm;
- Matrix: approximately 14- x 256. The number of phase-encode lines will depend on the exact sequence used;
- Inter-slice gap: 3mm;
- Series: interleaved;
- Number of acquisitions: 1;
- Phase-encoding: L > R.

Please note that the hard copies of this first series of T1- or T2- axial images should be done only for the baseline scan and then used as a reference fore repositioning the second scan at the study termination visit.

Write the slice positioning parameters (shift and rotation angle) of this series and use them for the second scan this is not necessary if the scanner has a repeat or history function).

If possible, to speed up the examination, use a rectangular 3/4 FOV (*i.e.*, reduce the phase-encoding matrix by 25%) when doing all the subsequent series of axial images. When using 3/4 FOV, the FOV is 187.5 in L > R direction and 250mm in A > P direction; matrix is 256 (read) x 192 (phase).

The scanning procedure is resumed by doing two interleaved series of fast or turbo spin-echo dual echo sequence. Conventional spin-echo sequences are allowed in case fast imaging is not available.

Image parameters will be the as follows:

- TR: 2200-2800;
- TE: 15-50/80-120;
- ETL: 4-5;
- Slice number: 22;
- Slice thickness: 3mm;
- Orientation: axial;
- Field of view (FOV); 250mm;
- Matrix: 256 x 256 (192 x 256 if REC FOV);
- Inter-slice gap: 3mm;
- Series: interleaved;
- Number of acquisitions: 1
- Phase encoding: L > R;
- Re-saturation slab/flow compensations: Yes.

The axial pre-saturation slab (50-80mm) will be positioned inferior to the slice group to suppress flow-related artifacts.

The second series will have a slice position shifter 3mm caudally compared witht eh first one, so that when both series are combined, the whole brain is covered.

Some General Electric and Philips scanners allow all the two separate acquisitions (each of 22 slices) to be performed sequentially and automatically from a single prescription. If the scanner used allows the acquisitions to be split automatically in this way, then this should be done.

Perform a bolus injection of gadolinium-DPTA using the intravenous long-line and without moving the patient form the scanner. Use contrast at a standard dose of 0.1mMol/kg (*i.e.* 0.2ml/kg). During the post-injection delay interval the acquisition of additional sequences is allowed by negotiation with the MRI Steering Committee. After a post-injection delay of 5min, complete the canning with post-gadolimium T1-weighted SE images.

The following parameters should be used:

- TE: 15-50/80-120;
- ETL: 4-5;
- Slice number: 22;
- Slice thickness: 3mm;
- Orientation: axial;
- Field of vies (FOV): 250mm;
- Matrix: 256 x 256 (192 x 256 is REC FOV);
- Inter-slice gap: 3mm;
- Series: interleaved;
- Number of acquisitions: 1;
- Phase encoding: L > R;
- Re-saturation slab/flow compensation: Yes.

The second series will be positioned to fill the gaps of the fist one. Once the two acquisitions are completed, check the image consistency in terms of both correct repositioning (when compared with “fast” T1) and covering the whole brain as indicated above. In case of spoiled post-contract T1-weighted images due either to patient movement artifacts, or to a change in slice position of 6mm or more (*i.e.* > 2 slice thickness compared to baseline scan),k post-contrast T1-weighted sequence should be repeated within 20min after gadolimium DTPA injection.

When the scanning session of the MRI baseline scan is concluded, it is the responsibility of the treating neurologist to assess whether the abnormalities present on the MRI scans are compatible with MS (consultation with a local neuro-radiologist is advisable). If any other neurological condition is suspected on the basis of the MRI data, the patient will not be allowed to enter or to continue the study. Follow-up scans should be evaluated by the center radiologist and only non-MS changes may be discussed with the treating physician, if required.

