**Steroid Treatment and MRI Scan Schedule**

It is recognized that steroid therapy strongly reduces the effect of gadolinium-enhancement and to a minor degree, the size of lesion of T2-weighted images. However, moderate and sever MS relapses may warrant treatment with I.V. methylpredisolone (IVMP), as described in an earlier section of this appendix. There is no best solution to this problem. In this study, patients treated with IVMP will be scanned at pre-planned times, rather than to arbitrarily adjust for recent steroid use.

On the MRI scans obtained at the termination of the study (all patients), the following analysis will be performed:

- Count of total contrast-enhancing T1-weighted lesions;
- Quantification of enhanced lesion volume;
- Count of new hyper-intense T2 lesions;
- Quantification of hyper-intense T2 volume;
- Quantification of hypo-intense T1 lesion volume;
- Quantification of brain volume and atrophy.

Three experienced neuro-radiologists will be in charge of lesion identification and counting in the study. For each scan, two of them (the same for the same patients throughout the entire study duration) will assess abnormalities by consensual agreement. In case of persistent disagreement (between the two neuro-radiologists), a fourth senior observer will make the final decision. A single enhancing lesion is defined as an area of enhancement seen on a given 3mm axial image, which is referable neither to normally enhanced structures, nor to contrast migration within vessels. T2-weighted FSE/TSE images will be used as reference for analysis. A single T2 lesion is defined as an area of increased signal on a given 3mm axial image, which should be seen on both T2- and proton density weighted images and which is not referable to normally hyper-intense structures. New T2 lesions have to appear in areas where on the previous scan no abnormality was detected. A single hypo-intense T1 lesion is defined as an area on a given 3mm axial slice with a signal intensity between those of gray matter and CSF. New T1 hypo-intense lesions have to appear in areas where on the previous scan no discrete hypo-intense abnormality was detected. Lesions that are contiguous in adjacent 3mm axial slices will be counted only once.

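### Appendix IV orders the post-gadolinium scan as T1-weighted spin echo but gives it the dual-echo TE and echo-train values and no TR, so the acquisition behind two secondary MRI measures is not validly fixed

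*Protocol*

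**What the plan says.** Section 4 of the protocol lists among the secondary efficacy endpoints "The total number of T1-Gd enhancing lesions (in MRI) and of T1 hypo dance black holes". Section 7.4 adds the volumes of enhancing and of T1 hypo-intense lesions. The analysis list in Appendix IV, under the heading on steroid treatment and scan schedule, includes "Quantification of hypo-intense T1 lesion volume".

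Appendix IV sets out how the images are acquired. Its sequence list ends with "T1-weighted SE post-gadolinium", and the later instruction is to "complete the canning with post-gadolimium T1-weighted SE images". The parameters printed below that instruction are TE 15-50/80-120, ETL 4-5, 22 axial slices of 3 mm with 3 mm gaps, a 256 x 256 matrix and pre-saturation/flow compensation. No TR is listed.

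Two other blocks matter for comparison:

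- The dual-echo block, introduced by "The scanning procedure is resumed by doing two interleaved series of fast or turbo spin-echo dual echo sequence", comes just before the gadolinium injection.
- The T1 block, introduced by "For T1-weighted images, the following parameters should be used", gives TR 600, TE 10-20, no ETL and a 140 x 256 matrix. It belongs to the pre-contrast positioning check, which the sequence list describes as "Rapid T1-weighted SE or T2-weighted FSE/TSE axial scout (this is for repositioning check"). That check may therefore be T1 or T2, at the site's choice.

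**The concern.** The name of the scan and its numbers describe different sequences. An operator who follows the name runs a T1 spin echo and has to choose TR, TE and the rest without guidance. An operator who follows the numbers runs a two-echo fast spin echo, again with TR left to choice.

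Both T1-based measures depend on image weighting. Enhancement is read on T1 images after contrast. Appendix IV defines a hypo-intense T1 lesion by signal between that of grey matter and CSF, so the lesion definition itself assumes T1 contrast. The appendix also judges new T1 hypo-intense lesions against the previous scan, taken 12 months earlier. If the two scans are acquired with different settings, a change in count or volume may reflect the settings rather than the disease. Images acquired with the wrong weighting cannot be recovered afterwards.

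**Working it through.** The protocol states no figure to reproduce here. The check sets the parameter blocks of Appendix IV side by side, then works out slice coverage.

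**1. Post-gadolinium block against the other two blocks**

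| Item | T1 block (positioning) | Dual-echo block | Post-gadolinium block |
|---|---|---|---|
| TR | 600 | 2200-2800 | not given |
| TE | 10-20 | 15-50/80-120 | 15-50/80-120 |
| ETL | none | 4-5 | 4-5 |
| Slices, thickness, gap | 22, 3 mm, 3 mm | same | same |
| Orientation, FOV | axial, 250 mm | same | same |
| Matrix | 140 x 256 | 256 x 256 (192 x 256 with rectangular FOV) | as dual-echo |
| Series, acquisitions, phase encoding | interleaved, 1, L > R | same | same |
| Pre-saturation/flow compensation | none listed | yes | yes |

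The dual-echo block has 13 lines and the post-gadolinium block has 12. All 12 carry the dual-echo values, and 13 - 12 = 1, the missing line being TR. Against the T1 block, the post-gadolinium block differs in TR, TE, ETL, matrix and pre-saturation. The first-echo range overlaps the T1 range only at 15-20. The second echo, 80-120, does not overlap it at all.

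**2. What the appendix uses elsewhere for each weighting**

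- T1 series: the three scouts have TR 100, 100 and 500-650, and the T1 positioning block has TR 600. All four have a single TE of 10-20 and no ETL.
- T2 and dual-echo series: the T2 positioning block has TR 1800-2000, an optional second echo at 60-100 and an ETL line. The dual-echo block has TR 2200-2800, a second echo at 80-120 and ETL 4-5.

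By the appendix's own usage, an echo train and a late second echo belong to the T2 and dual-echo group. Taken literally, these TE and ETL values do not describe a T1-weighted SE scan.

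**3. Whether another prescribed series could stand in**

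- The T1 scouts have 3, 1 and 1 slices. They are mandatory but do not cover the brain.
- The positioning series is pre-contrast and need not be T1. It is a single series. Tissue imaged: 22 x 3 mm = 66 mm. Slab spanned: 22 x 3 mm + 21 gaps x 3 mm = 129 mm. Fraction: 66/129 = 51%.
- The post-gadolinium acquisition uses two series, the second filling the gaps of the first: 44 x 3 mm = 132 mm.

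The post-gadolinium acquisition is therefore the only post-contrast one prescribed and the only mandatory T1 acquisition that covers the whole brain.

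**4. Scans governed by the instruction**

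30 patients x 2 scans (baseline and termination) = 60, ignoring drop-outs and any replacements.

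**The case against.** A reader might infer that anyone following Appendix IV would acquire no valid T1 images, and that all 60 scans would be lost. The document does not support that. The appendix names the scan as T1-weighted in its opening line, in the sequence list, in the instruction itself and in the rule for repeating spoiled images. With TR missing, the block does not fully define a dual-echo scan either. The operator meets a visible contradiction and could resolve it by running the named T1 scan.

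The setting also lowers the risk. The trial has one site and one stated scanner. Section 15.1.3 gives a radiologist responsibility for evaluating the results, section 7.4 provides for a blinded MRI analysis centre, and section 14.2 plans a study manual with procedures that are not shown here.

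One more passage helps in part. The post-acquisition check compares positions with the fast T1 series, which presupposes that a T1 positioning series was run. Such a series could bear on black holes, though only before contrast and over about half the slab; it cannot show enhancement. That black holes are read from the post-gadolinium images is itself an inference. It is plausible because the appendix opens by naming only post-contrast T1 and dual-echo scans.

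These points limit the consequence. They do not remove the defect: the protocol nowhere corrects the block, and the stated triggers for repeating the scan are movement and slice shift, not wrong weighting.

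**Conclusion.** The point holds as an internal contradiction and an omission. The post-gadolinium block conflicts with its own sequence name and with every T1 setting in the appendix, and it gives no TR. The acquisition for enhancing lesions and T1 black holes is therefore not validly fixed, and the two scans of one patient could be acquired differently.

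The 60 scans are those governed by the faulty text, an upper bound on those affected and not a count of invalid images. Reaching that bound assumes the TE and ETL values are followed literally every time. Only T1-based secondary MRI measures are at risk. The primary EDSS endpoint, the relapse counts, the T2 lesion measures and the sample size are untouched. The point is still worth correcting before any scan is made, because the loss would be irreversible.

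**What to change.** Before the first scan, reconcile the sequence list and the parameter blocks of Appendix IV:

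- Replace the copied TE and ETL lines under the post-gadolinium instruction with a single-echo T1 spin-echo specification, and state a TR.
- Take the appendix's own T1 block as the natural starting point, with the values to be confirmed by the trial's MRI radiologist. That block was written for a rapid positioning check at lower matrix, and nothing says it was meant to govern the lesion scan.
- Keep the slice geometry and the two interleaved series.
- Require identical values at baseline and at termination.
- State which series is used to read T1 hypo-intense lesions.

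The cost is a wording correction to the appendix. It needs no extra patients or procedures.
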